## Abstract

**Introduction:**

One of the main harms from breast cancer screening is the anxiety caused by false positive results. Various factors may be associated with false-positive anxiety. One modifiable factor may be the method of communication used to deliver results. The aim of this study is to measure the effect on anxiety of receiving benign biopsy results in-person or by telephone.

**Methods and analysis:**

This is a multi-centre cluster randomised crossover trial in the English National Health Service Breast Screening Programme (NHSBSP) involving repeated survey measures at four time points. Participants will be women of screening age who have a biopsy following a suspicious mammography result, who ultimately receive a benign or normal (B1) result. Centres will trial both telephone and in-person results on a month-by-month basis, being randomised to which communication method will be trialled first. Women will be blinded to the method of communication they will receive. The analysis will compare women who have received telephone results and women who have received in-person results. The primary outcome measure will be anxiety (measured by the Psychological Consequences Questionnaire) after receiving results, while controlling for baseline anxiety. Secondary outcome measures will include anxiety at 3 and 6 months post-results, understanding of results and patient preferences for how results are communicated. Qualitative telephone interviews will also be conducted to further explore women’s reasons for communication preferences. Qualitative and quantitative data will be integrated after initial separate analysis using the pillar integration process.

**Ethics and dissemination:**

This study has been approved by the Public Health England Breast Screening Programme Research Advisory Committee, (BSPRAC_0013, ODR1718_040) and the National Health Service Health Research Authority (HRA) West Midlands—Coventry & Warwickshire Research Ethics Committee (17/WM/0313). The findings from this study will be disseminated to key stakeholders within the NHSBSP and via academic publications.

**Trial registration number:**

ISRCTN36997684

**Trial sponsor:**

This research is part of a PhD award and is funded by the Economic and Social Research Council Doctoral Training Centre at the University of Warwick and Public Health England. The sponsor for this research is [name] ([contact]).

Strengths and limitations of this studyThis is the first cluster randomised crossover trial to measure the impact of communication method on patient outcomes when delivering results in breast screening.The mixed-methods design adds depth to our understanding of communication preferences and the mechanisms by which anxiety may be affected.The study is in English breast screening centres and generalisability to other contexts should be carefully considered.

## Introduction

The UK National Health Service Breast Screening Programme (NHSBSP) is a population-based screening programme that aims to detect early signs of breast cancer. Asymptomatic women aged 50–70 are invited to attend every 3 years for a mammogram. The results of the mammogram take a maximum of 2 weeks as per NHSBSP guidelines.^1^ If a suspected abnormality is found on the mammogram then the woman is invited back to the clinic for follow-up tests, usually within the next 2 weeks.

Follow-up tests can include clinical examination, a further mammogram or ultrasound. If these indicate suspicion of cancer then the woman receives a core needle biopsy, involving the removal of sections of tissue from the suspicious breast region. This tissue can then be pathologically analysed. Although the procedure is designed to be minimally invasive, leaving only minor bruising, some women find the experience painful and distressing. It is standard practice to perform all follow-up tests (clinical exam, mammogram, ultrasound and biopsy) on the same day in an assessment clinic to avoid unnecessary extra waiting time for patients. Results of diagnostic tests are discussed on a case-by-case basis at multidisciplinary team meetings using a triple-assessment of clinical examination, imaging and biopsy report. Clinical guidelines recommend that all follow-up results should be delivered to the woman within 1 week.^2^ These results are delivered by either telephone or in-person, depending on the procedure at the breast screening centre.

Screening programmes should provide benefit that outweighs both physical and psychological harm.^3 4^ One of the main harms from breast screening is the anxiety caused by false positive results.^5^ A false-positive result is when a woman has been identified at the screening phase as potentially having cancer, but follow-up tests have revealed no abnormalities. Receiving a false-positive result from screening is very common, with the majority of women who are recalled ultimately being given a false-positive result.^6^ In England, around half of women receive the all clear results at the time of the follow-up tests. Women who are invited to be screened have no symptoms of breast cancer at the time of their initial mammogram. Telling a woman that something suspicious has been found in the mammogram and that further tests are needed can make her feel very anxious and believe that she might have cancer.^7^ For some women, once results confirm the absence of cancer, anxiety declines. However, anxiety can remain elevated for much longer, lasting up to 3 years after receiving the benign result and leading into the next screening invitation.^8^ This is an issue, as the NHSBSP has a duty to minimise the harm caused by screening.

There are various factors that may be associated with heightened anxiety during screening such as family history, lower education, younger age and individual differences in personality.^1 9–13^ These factors are unmodifiable and tend to be focused at the level of the individual, which makes the minimisation of screening anxiety a challenge. However, it is possible that there are modifiable changes that can be made at the organisational level of screening that may minimise the impact of anxiety. One of these changes is the method of communication used to deliver results.

NHSBSP guidelines for communicating results state that telephone results ‘should not be routinely offered’.^14^ However, most breast screening centres in the UK deliver benign results to the woman over the telephone. Some breast care nurses remain concerned about how the communication method used to deliver results may contribute to the anxiety experienced by women attending screening.^2^ Telephone results may offer advantages, eliminating the stress and costs associated with transport, parking and anxiously waiting in a clinic for results. However, telephone results eliminate the in-person encounter, meaning all communication is verbal only. Research from other areas has shown that non-verbal communication plays a key role in enhancing understanding and minimising anxiety.^15^

The communication methods used to deliver benign results in the NHSBSP have not yet been explored. Therefore, the impact of this communication on women receiving a benign result is unknown.

### Aim of the study

The aim of this study is to compare anxiety in women receiving benign biopsy results from the NHSBSP via telephone results or in-person.

## Methods and analysis

### Study design

The study design chosen was a multi-centre cluster randomised crossover trial. The randomisation allows for the direct comparison of study outcomes between women who received telephone results and women who received in-person results, while controlling for confounding factors such as education, age and individual differences in baseline anxiety.

Patient and public involvement from the charity Independent Cancer Patients’ Voice was used to guide the design of the study to ensure the acceptability of the method and appropriateness of the participant materials.

### Participants and settings

This trial will be conducted in a breast screening centre setting. The study will take place in the UK where women are invited to attend breast screening every 3 years for digital mammography. The study will take place across four time points (see table 1) with a survey completed by participants at each stage. The study participants will be recruited from four English Breast Screening centres across different regions.

**Table 1 T1:** Time points for the study

Time point	Sample	Survey content	Method
Time point 1—at assessment clinic	Women attending assessment follow-up clinic	Demographic information Communication preferences Baseline anxiety score (PCQ) Contact details	In-person
Time point 2—after receiving results	Women from time point 1 who had a normal or benign biopsy	Communication preferences Repeat anxiety score (PCQ) Measure of understanding	By post
Time point 3—3-month follow-up	Women from time point 1 who had a normal or benign biopsy	Repeat anxiety score (PCQ)	By post
Time point 4—6-month follow-up	Women from time point 1 who had a normal or benign biopsy	Repeat anxiety score (PCQ)	By post

PCQ, Psychological Consequences Questionnaire.

Participants will be women between the ages of 47 and 73 attending the NHSBSP for further tests following a suspicious mammogram. This includes women offered routine screening between ages 50 and 70 and those receiving extra rounds of screening between the ages of 47 and 49 or 71 and 73 as part of the UK age extension trial.^16^ Women will be recruited at the assessment clinic pre-biopsy. However, only women who have received a benign (B2) or normal (B1) biopsy result will be included in the longitudinal data collection. Participants will not be included in the study if they presented symptomatically to the breast clinic, if they are not the recommended screening age, if they do not receive a biopsy, if they do not have English as a first or second language and if they do not have the capacity to consent.

### Measuring anxiety

The Psychological Consequences Questionnaire (PCQ) was selected as the most appropriate measure of anxiety in the breast screening setting^17^ and was embedded in the participant surveys (see online supplementary appendix 1). The PCQ is a disease-specific measure, focusing on breast cancer specific anxiety across 12 questions on three dimensions: emotional, social and physical anxiety. The disease-specific measure avoids the contrast validity that is associated with using generic anxiety measures in the breast screening context.^18^ The PCQ is widely used in the breast screening setting.^1 8 19–21^

10.1136/bmjopen-2018-028679.supp1Supplementary data

Participants will rate their anxiety on the PCQ by judging each statement on a scale of 0 (not at all) to 3 (quite a lot of the time). Women will be asked “*Over the last week* how often have you experiences the following things because of *thoughts and feelings about breast cancer:”*

### Randomisation and blinding

Each centre will be randomised to one of two intervention arms by computer generated random numbers from the trial team base at the University of Warwick (see table 2). The arm relates to whether the first month at each centre will be telephone or in-person results. Each centre will commence with the communication method randomised in month 1 and continue to alternate between the two communication methods for the duration of the study. This approach allowed for each centre to use both methods of communication, controlling for previous experience (eg, centres who already telephone are more experienced and therefore women receiving telephone results from this centre might be less anxious).

**Table 2 T2:** Allocation of communication method by arm of the trial

Month	Arm 1	Arm 2
1	Telephone	In-person
2	In-person	Telephone
3	Telephone	In-person
4	In-person	Telephone
5	Telephone	In-person
6	In-person	Telephone

This approach was selected instead of a block approach, where each centre would deliver 6 months in-person followed by 6 months of telephone. The reason for this was to avoid potential bias from unforeseen centre drop out.

This design was chosen to ensure balance between trial arms at each site while addressing practical constraints. Balance between trial arms at each site is important to account for centre-level confounders such as staff communication skills and centre-level processes.

Individual randomisation was not possible as it interfered with screening centres workflow and fail-safe mechanisms to ensure that every woman was contacted with the correct information within the correct time frame.

Women will be allocated to receive their result based on the date of their attendance at the assessment visit. However, participants will be blinded to the randomisation month. Participants will only become aware of the communication method allocated when the results are received (see ‘Allocation of communication method’ section below for further detail). Breast screening staff will not be blinded, as they will be delivering the results and scheduling the appointments.

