### Allocation of communication method

There are two types of centres who may be involved in the research: centres who currently deliver benign results in-person and centres who currently deliver benign results by telephone.

For centres currently delivering results in-person, the following process for scheduling a results appointment will be observed: During in-person study months, all consenting women at time point 1 will be given an appointment to re-attend to receive their results in-person and will receive the result in-person. During telephone study months, all consenting women at time point 1 will be given an appointment to re-attend to receive their results in person. However, they will instead be telephoned prior to their scheduled appointment. Only benign women will be telephoned, with all women receiving other results (eg, cancer) attending their scheduled appointment.

For centres currently delivering results by telephone, the following process for scheduling a results appointment will be observed: All consenting women will be informed that, when their results are ready, they will be contacted by telephone to arrange an appointment to come back for their results. During the ‘telephone’ months of the study, women will be telephoned as expected. However, instead of arranging an appointment during this telephone call, results will be delivered. This means that, for women who go on to have a cancer result, they can be telephoned to arrange an appointment to attend in-person, as expected. This is in line with standard practice at these centres. During the in-person months, all consenting women will be informed that, when their results are ready, they will be telephoned to arrange an appointment to come back for their results. These women will be telephoned to arrange an appointment to come back in-person, and at that appointment they will receive their benign/normal result.

All women not enrolled in the study will receive their screening result based on the current standard practice at the attended centre.

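### Women are said to learn the delivery method only with the result, but at telephone centres in-person-month women can learn it from a prior booking call, and only the telephone arm departs from the visit announced

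*Protocol article*

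**What the plan says.** The abstract of the protocol article (*Methods and analysis*) makes an unqualified claim: "Women will be blinded to the method of communication they will receive". The section *Randomisation and blinding* adds that "participants will be blinded to the randomisation month" and then states: "Participants will only become aware of the communication method allocated when the results are received". It refers the reader to *Allocation of communication method* for detail.

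That section describes two types of centre.

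- **Centres that normally give results in person.** All consenting women leave the assessment visit with an appointment. This includes women in the other arm: "During telephone study months, all consenting women at time point 1 will be given an appointment to re-attend to receive their results in person". For those with a benign result the plan then changes: "However, they will instead be telephoned prior to their scheduled appointment".
- **Centres that normally telephone.** In both kinds of month, women are told that "they will be contacted by telephone to arrange an appointment to come back for their results". In telephone months, "instead of arranging an appointment during this telephone call, results will be delivered". In in-person months, "These women will be telephoned to arrange an appointment to come back in-person, and at that appointment they will receive their benign/normal result".

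*Aim of the study* presents the comparison as telephone against in-person delivery. The primary outcome is the PCQ score at time point 2, and under *Measuring anxiety* the PCQ asks about the previous week.

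**The concern.** The masking statement covers every participant, yet the procedure it points to includes a contact, before the result and in one arm only, that shows how the result will be given. The outcome is self-reported anxiety, so a reader will give weight to a statement that women did not know their method until the result arrived. If a report repeats that statement, it will be untrue for part of the in-person arm wherever a telephone centre takes part.

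The second issue is what the contrast measures. Every woman is led to expect a visit. In-person women get what was announced, and telephone women do not. At telephone centres the in-person arm also has a call without a result and a further wait. These features change with the method inside each centre. Alternating months, and the centre and period effects in the primary model, therefore cannot separate them from the method. The findings are meant to inform programme policy, where telephone results would naturally be read as a service that women have been told to expect.

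**Working it through.** The plan gives no figure to reproduce on this point. The check sets the masking sentence against each pathway in *Allocation of communication method*.

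| Centre normally | Study month | Told at assessment | What then happens (benign or normal result) | Method can be known before the result? | Result given as announced? |
|---|---|---|---|---|---|
| In person | In-person | Appointment to return | Result at that visit | No earlier contact described | Yes |
| In person | Telephone | Appointment to return | Result by telephone before the appointment | No | No |
| Telephone | Telephone | A call will arrange a visit | That call gives the result | No | No |
| Telephone | In-person | A call will arrange a visit | Call books the visit, result follows at the visit | **Yes** | Yes |

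**Masking.** The sentence in *Randomisation and blinding* is consistent with three pathways and fails in the fourth. The failure is always in the in-person arm.

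**Consent and baseline.** Within each centre type, what women are told at assessment is the same in both kinds of month. The time point 1 survey is collected before they leave the clinic. Masking up to that point is therefore supported.

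**Announcement.** The last column follows the method exactly: both in-person pathways are as announced and both telephone pathways are not. At telephone centres the telephone arm does receive the call it was told to expect. What departs from the announcement is that the result comes in that call.

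**Contact and timing.** At telephone centres, in-person women have one more contact than telephone women, and a wait between call and visit. At in-person centres, telephone women get the result earlier than the appointment they were given.

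**How many women could be affected.** The planned number at time point 2 is 290 (*Sample size considerations*). Assume an equal split by method, 290 / 2 = 145 in-person women, and four centres of equal size. With k telephone centres, the number in the fourth pathway is 145 × k/4:

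- k = 0: 0 women (0% of the in-person arm)
- k = 1: 36.25, about 36 (25%)
- k = 2: 72.5, about 73 (50%)
- k = 3: 108.75, about 109 (75%)
- k = 4: 145 (100%)

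The article says only that both types of centre may be involved, so k = 0 cannot be excluded. These figures count women exposed to a prior booking call. They say nothing about the effect on the PCQ.

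**The case against.** The strongest reply is that the booking call is set out openly, in the section the masking sentence points to. The call does only what women were told it would do, so it confirms an expectation and springs no surprise. Telling all women the same thing is deliberate: it keeps them masked at consent and baseline, and at telephone centres it lets women with a cancer result be called to attend as they were told. Arranging a visit and waiting for it can also be seen as part of in-person delivery, and comparing whole delivery routes is a legitimate pragmatic question.

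Much of this stands. Baseline masking is intact, the announcement procedure has a good reason, and a comparison of pathways is worth making. But the pointer leads to the contradiction without resolving it. A woman who has been called to book a visit can know the method before the result, even if the call only confirms what she was told. And if the comparison is of pathways, the conclusion should say so.

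A reader might go further and infer that the early call raises in-person scores and so biases the trial. If, say, the call added 1 to 3 points in affected women and 25% to 75% of the arm were affected, the contrast would move by 1 × 0.25 = 0.25 to 3 × 0.75 = 2.25 points, against a target difference of 3. The documents support neither the direction nor the size. The mix of centres is not stated and may include no telephone centre. The PCQ covers one week and the survey is postal with a reminder only after a week, so the recall window of a late responder may miss the call altogether.

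**Conclusion.** The point holds as an internal contradiction and a limit on interpretation, not as a demonstrated bias. The unqualified masking claims in the abstract and in *Randomisation and blinding* are wrong for one of four pathways, in the in-person arm only, and matter in practice only if at least one of the four centres is a telephone centre. The share of that arm affected could be anything from 0% to 100% under the equal-size assumption. The effect on the PCQ is unknown in direction and size.

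That only telephone women depart from what was announced holds for either type of centre, so this part does not depend on the mix. It does not itself break the masking, but it limits what the contrast can be said to show.

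A reader might infer that masking fails throughout, or that restricting to in-person centres would give a clean masked comparison. Neither follows. Masking at consent and baseline is supported. In the restricted set the timing of the result still differs between arms, the departure from the announced visit remains in full, and the number of such centres is unknown and could be none or one.

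**What to change.** 1. Reconcile the abstract, *Randomisation and blinding* and *Allocation of communication method*. Limit the masking claim to the period up to the first contact after the assessment visit. Say that women are masked at consent and at the baseline survey, and that in in-person months at telephone centres they are not masked until the result.
2. Describe the comparison, and state the conclusion, as one of delivery pathways (method together with its timing, any prior call, and any departure from what was announced) in women told to expect a return visit. Do not present it as the effect of method alone or of an announced telephone service.
3. When reporting, give the number of centres of each type so that readers can see how far the exception reaches. An estimate by centre type may be shown as descriptive only, without the label of a masked comparison.

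The cost is wording in the protocol, the analysis plan and the eventual report, plus at most one descriptive table from data already being collected. The article says a detailed analysis plan will be written before recruitment is complete, so the wording can be settled there. No trial procedure needs to change.

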### Data collection

#### Time point 1

Participant recruitment at time point 1 will occur concurrently at each breast screening centre.

Women will be approached during their assessment visit by breast care nurses with good clinical practice training. These women would have been recalled from a previous mammogram and may have a biopsy as part of the assessment clinic. The study will be explained to potential participants and nurses will go through the informed consent process. Consenting women will fill out the time point 1 survey with study responses collected and stored securely before the participant leaves the assessment clinic.

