**Figure 1 F1:**
[figure not shown]
Flow of required sample size for the study.

Assuming the primary outcome is approximately normally distributed, and the test is at the 5% significance level with 80% power to detect an effect of the specified size, 194 participants are required at time point 2, that is 97 participants per arm. Allowing for attrition rate between time point 1 and time point 2 due to participant withdrawal (15%) and participant eligibility (50%), a total of 457 participants will be recruited at time point 1. Participant withdrawal was calculated based on a mean response rate of 60% from previous research using postal surveys in a medical setting^24^ with a loss of 15% at each time point as a conservative estimate.

In order to account for clustering due to the recruiting centre, design effect was applied that inflated the sample size. The intra-cluster (within-centre) correlation coefficient was set to be 0.01 and the number of observations within each cluster was assumed to be equal. With the sample size of 194 women, divided by the number of centres^4^ and then divided by the number of interventions,^2^ this led to the number of observations within a cluster to be 48.2. This gave a design effect of 1.49. Taking this into account, the sample size needed to achieve statistical significance (194 women) was multiplied by the design effect, giving a total sample of 290 women at time point 2 when rounded up (see figure 1).

31 926 women are recalled for a biopsy each year. If half of the 31 926 biopsies come back as benign, this leaves a potential sample of 15 963. This means that, on average across 80 breast screening centres, each centre will have around 200 benign biopsy results each year. Therefore, assuming 50% participation rates of eligible women, recruitment will require four centres for 1 year.

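### Nurses who take consent know the month's method, which they do not need at that stage, so enrolment could differ by method and the plan described would not reveal it

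*Protocol article*

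**What the plan says.** Under Randomisation and blinding, only the first month at each centre is random: "Each centre will commence with the communication method randomised in month 1 and continue to alternate between the two communication methods". A woman's method follows from the calendar: "Women will be allocated to receive their result based on the date of their attendance at the assessment visit". Women are blinded until they get the result. Staff are not: "Breast screening staff will not be blinded, as they will be delivering the results and scheduling the appointments".

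Under Data collection, Time point 1: "Women will be approached during their assessment visit by breast care nurses with good clinical practice training". The same nurses take consent.

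Under Allocation of communication method, a centre that normally gives results in person books every consenting woman to return, whatever the month: "During telephone study months, all consenting women at time point 1 will be given an appointment to re-attend". A centre that normally telephones tells every consenting woman, in both kinds of month, that she will be called to arrange a visit. The same section adds: "All women not enrolled in the study will receive their screening result based on the current standard practice at the attended centre".

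The Introduction reports that some breast care nurses worry about how the method may affect anxiety. Sample size considerations plans recruitment "assuming 50% participation rates of eligible women".

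**The concern.** Randomising centre-months makes the women attending in telephone and in-person months comparable. It does not make the women enrolled comparable if the person deciding whom to approach knows the method. A nurse who would rather not use the non-standard method for a visibly distressed woman need only not enrol her that month, and she then gets the usual method. Perceived distress is close to the primary outcome, so selection of this kind would shift the time point 2 PCQ difference directly. Adjustment for time point 1 PCQ removes only the part of that shift which the baseline score carries.

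Scheduling is one of the two reasons given for not blinding staff, and it does not apply at the moment of consent, because the booking or statement at the visit is the same in both kinds of month.

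**Working it through.** **1. Is the method needed at consent?**
- In-person centres: a return appointment is given in both kinds of month. In telephone months the woman is called before it.
- Telephone centres: the same statement is made in both kinds of month. The later call either gives the result or arranges a visit.

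The months therefore diverge only after the multidisciplinary meeting has identified the B1/B2 women.

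**2. Which way would selection push?** Enrolment changes the method received only in telephone months at in-person centres and in in-person months at telephone centres. Omitting distressed women in those months flatters telephone at the first type and in-person at the second. The mix among the four centres is not stated.

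**3. Size, under assumptions.** The article gives no SD. Solving n per arm = 2·SD²·(1.96 + 0.84)²/3² for the stated 97 per arm (two-sided 5%, 80% power) gives an SD of about 7.42 to 7.46; 7.42 is used. Assume that:
- a fraction p of women, those seen as most distressed, is omitted in one method's months at every centre;
- perceived distress correlates 0.5 with time point 1 PCQ, and time point 1 correlates 0.5 with time point 2;
- perceived distress correlates r with time point 2 PCQ.

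Removing the top p of a normal variable lowers its mean by λ = φ(z)/(1 − p) standard deviations, with z the (1 − p) quantile: 0.109, 0.195 and 0.350 for p = 5%, 10% and 20%.

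Unadjusted shift = r × 7.42 × λ. For r = 0.5 this is 0.40, 0.72 and 1.30 points.

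Shift after baseline adjustment = (r − 0.5 × 0.5) × 7.42 × λ.

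SE = 7.42 × √(1 − 0.5²) × √(4/290) = 0.755. Type I error = P(|Z + bias/SE| > 1.96).

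| r | Adjusted bias at p = 5%, 10%, 20% | Type I error |
|---|---|---|
| 0.25 | 0, 0, 0 | 5%, 5%, 5% |
| 0.4 | 0.12, 0.22, 0.39 | 5.3%, 6%, 8.1% |
| 0.5 | 0.20, 0.36, 0.65 | 5.8%, 7.7%, 13.8% |

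A simulation that re-estimates the baseline slope in the selected sample moves the largest bias slightly, to just under 0.7 points, with type I error just under 15%.

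**4. Sensitivity, at r = 0.5.**
- Only half the women in affected centres: the bias halves to 0.10, 0.18 and 0.32, and type I error is 5.2%, 5.7% and 7.1%.
- Precision of 194 independent women, since 290 is 194 inflated for clustering: SE = 7.42 × √0.75 × √(4/194) = 0.923, and type I error is 5.6%, 6.8% and 10.8%.

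**The case against.** A reader might infer that scheduling never depends on the month, so that the stated reason for not blinding staff is simply wrong. The article does not support that. At telephone centres the later call arranges a visit in in-person months and gives the result in telephone months, and those who deliver results must know the method. The stated reason is accurate for staff as a group. What stands is narrower: the article does not separate recruiting from delivering, and the recruiting step does not need the method. It does not show that separate people would be feasible, and it cites workflow and fail-safe limits when ruling out individual randomisation.

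A reader might also infer that nurses did select, or that telephone was favoured. Neither is shown. The Introduction reports concern among some nurses, not unwillingness to enrol. The 50% participation is a planning figure that also covers women's own refusals. If nurses simply avoid the unfamiliar method, the two centre types push in opposite directions and partly cancel.

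The safeguards count. Blinded women cannot select themselves by method, recruitment before biopsy prevents selection on the result, each centre is its own control, and the model includes baseline PCQ and six covariates, which the calculation ignores beyond PCQ. If perceived distress predicts the outcome only through baseline PCQ (r = 0.25), adjustment removes the bias entirely. None of these safeguards prevents a nurse from selecting on distress that the baseline score misses.

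Routine reporting of enrolment could sit in a fuller protocol or analysis plan. The finding therefore rests on what the article fixes: unblinded recruiters, a predictable sequence, and usual practice for women not enrolled.

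**Conclusion.** The concern holds as an open route to selective enrolment, not as evidence of bias. Consent is taken by unblinded nurses after a predictable method is set, at a point where they do not need to know it, and not enrolling a woman alters her care only in non-standard months.

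Under the assumptions above, the bias left after baseline adjustment is 0 to about 0.7 points, at most about 23% of the 3-point target, with type I error between 5% and about 14%. The upper end needs 20% of women omitted at all four centres in the same direction and r = 0.5; with half the women affected it is about 7%. The omission rates, correlations and direction are assumptions, and the SD is back-solved. This is a modest risk that deserves a cheap check and does not call for a redesign.

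**What to change.** 1. **Uniform approach and counts (the main step).** Have nurses offer consent to consecutive eligible women with one script. At the multidisciplinary meeting, record for each centre-month the number of all B1/B2 screening women and the number enrolled, and compile past months from centre records where possible. Compare enrolment fraction and time point 1 PCQ by allocated method within centre, and qualify the primary conclusion if they differ.

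   Report these as estimates with intervals, because small selection would not show. At about 200 benign results per centre-year, four centres give roughly 400 women per method. Omitting 20% would lower enrolment from 50% to 40%, with SE √(0.25/400 + 0.24/400) = 3.5 percentage points, which is visible. Omitting 5% would lower it only to 47.5%, which is not.

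2. **Partial concealment for any remaining months (a supplement).** Release the method to a centre only once the month's first B1/B2 list is received, and draw the order at random within each two-month pair in place of strict alternation. Each pair still holds both methods, so the protection against centre drop-out is kept. The gain is small. Results are due within a week, so staff soon learn the month's method, and the second month of a pair can be deduced; concealment covers about the first week in eight. With recruitment open since February 2018 and data collection ending in March 2019, few months may remain.

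**Cost:** two counts per centre-month, a new random list, and shorter notice to centres for planning results clinics. No extra staff are needed.
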